## Abstract

Disruptions in cognitive function have been reported in individuals undergoing haemodialysis and those with chronic kidney disease. This pilot study protocol primarily assesses the feasibility and acceptability of using mobile cognitive gaming apps for patient-led cognitive training during haemodialysis sessions. The protocol consists of three phases: (1) reviewing and evaluating available cognitive gaming apps, (2) conducting focus groups/interviews with people with kidney disease to determine app preferences, and (3) undertaking a quasi-experimental randomised controlled trial to compare cognitive outcomes between a patient-led app intervention group and a standard care control group over four months. Primary outcomes will include changes in cognitive test scores [Montreal Cognitive Assessment (MoCA), Modified Mini-Mental State Exam (3MSE), Rapid Objective Working Memory Assessment (ROWMA)], while secondary outcomes will encompass quality of life measures [Patient-Reported Outcomes Measurement (PROM) Kidney Disease Quality of Life Short Form (KDQoL-SF™) v 1.3, Patient-Reported Outcomes Measurement Information System (PROMIS) Global Health Instrument, European Quality of Life Five Dimension (EQ-5D)]. If demonstrated to be effective, this novel method of utilising gamified cognitive training applications could potentially mitigate cognitive decline and improve the well-being of people receiving haemodialysis without necessitating significant clinical resources. The findings from this research will guide the development of a larger definitive randomised trial in the future.

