## Methods and analysis

### Trial design

This trial is a single-centre, two-armed pseudo-randomised controlled pilot trial to assess the feasibility and effectiveness of patient-led CGT intervention for slowing cognitive decline in people receiving haemodialysis. This trial will contain three phases. Phase one will conduct a review and evaluation of CGT apps in the marketplace. The outcome of Phase one is to have a shortlist of CGT apps for the next phase by evaluating cognitive training apps. Phase two will assess and select CGT apps for the intervention phase by conducting semi-structured interviews with the haemodialysis patient focus group involving representatives from the Kidney Patient Associations (KPAs), people with kidney disease, and Kidney Care UK. Phase three will be a pseudo-randomised controlled study in which people receiving haemodialysis will undertake CGT intervention by engaging CGT apps during haemodialysis sessions. The outcome of Phase three will be to have comparisons of baseline and four-month follow-up assessments between the intervention group, which receives CGT apps, and the control group, which only has standard care. The trial flow diagram is presented in Fig. 1.

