### Outcomes

The primary outcome will be a change in cognitive test results (MoCA, 3MSE and ROWMA) of the intervention group at approximately four-month (± two weeks) follow-up assessments compared to the baseline assessments. The secondary outcomes will be the change in the behavioural test scores (PROM KDQoL-SF™ v1.3, PROMIS Global Health Instrument and EQ-5D questionnaires) for the CGT intervention group compared to the control group. The following validated instruments will be used to assess cognitive function, quality of life, and general health and well-being:

MoCA: A sensitive screening tool for mild cognitive impairment, assessing various cognitive domains including attention, concentration, executive functions, memory, language, visuoconstructional skills, conceptual thinking, calculations, and orientation^31^.3MSE: An expanded version of the MMSE that provides a comprehensive and sensitive measure of global cognitive function^32^.ROWMA: A brief, computerised test specifically designed to assess working memory, which is often impaired in patients with kidney disease^33^.KDQoL-SF™: A kidney disease-specific measure of health-related quality of life that includes generic core plus disease-specific domains such as symptom/problems, effects of kidney disease on daily life, burden of kidney disease, cognitive function, and dialysis staff encouragement^34^.PROMIS Global Health Instrument: A brief, generic self-report measure of health-related quality of life that assesses physical, mental, and social health^35^.European Quality of Life 5-D (EQ-5D): A standardized instrument for measuring generic health status, providing a simple descriptive profile and a single index value for health status^36^.

Table 2 provides a summary of these assessment tools, including their functions, score ranges, administration details, and other relevant information.

**Table 2 Tab2:** Summary of assessment tools.

Assessment tool	Function/rationale	Score range and interpretation*	Administration timing	Time to complete	Other details
Montreal Cognitive Assessment (MoCA)	Screens for mild cognitive impairment	0–30; ≥26 normal	Baseline and 4 months	10–15 min	Assesses multiple cognitive domains
Modified Mini-Mental State Exam (3MSE)	Comprehensive measure of global cognitive function	0-100; higher scores indicate better cognitive function	Baseline and 4 months	10–15 min	More sensitive than standard MMSE

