### Statistical analysis

Given the pilot nature of this study, our sample size is not based on formal power calculations. Instead, it is pragmatically determined by the number of eligible patients in our dialysis unit. The results will be used to estimate effect sizes and inform sample size calculations for a future, full-scale randomised controlled trial.

In Phase three, data will be analysed to test the effect of CGT intervention on the scores of baseline and follow-up assessments. All data analyses will be conducted in IBM SPSS Statistics for Windows, version 27.0 (or higher) software. Data will be directly entered into Microsoft Office Excel spreadsheets (version 2202) by investigators and study staff using all standard data management procedures. Descriptive statistics will be calculated according to the normality assumption, with means and standard deviations reported for normally distributed data, and medians and interquartile ranges reported for non-normally distributed data. Within-group comparisons between baseline and follow-up assessments for primary and secondary measurements will be analysed using repeated-measures analysis of variance (ANOVA). In contrast, independent ANOVA will be used for between-group comparisons. For additional explorative analyses, correlation and regression models can be used to analyse the effects of other factors (e.g. age, gender) on the cognitive decline between the baseline and follow-up assessments.

In addition to the primary and secondary outcome analyses, a sub-group analysis will be performed to explore the potential effects of the CGT intervention based on participants’ baseline memory function and executive function. Participants will be stratified into subgroups based on their performance on the cognitive test scores, and the intervention effects will be compared between these subgroups. This exploratory analysis may help to identify which patients are most likely to benefit from the CGT intervention and guide future research in this area.

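### The protocol contradicts itself on the primary cognitive contrast: the Outcomes section defines it within the intervention arm, other sections compare the arms, and the analysis section ranks neither

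*Protocol article*

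**What the plan says.** The Outcomes section gives the formal definition: "The primary outcome will be a change in cognitive test results (MoCA, 3MSE and ROWMA) of the intervention group", where the contrast is "follow-up assessments compared to the baseline assessments". The next sentence defines the secondary, quality-of-life outcomes as changes "for the CGT intervention group compared to the control group". The control arm is therefore named for the secondary outcomes and absent from the primary.

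Other parts of the article describe the cognitive contrast differently:

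- **Abstract:** Phase three is intended "to compare cognitive outcomes between a patient-led app intervention group and a standard care control group over four months". It also says "Primary outcomes will include changes in cognitive test scores", with no restriction to one arm.
- **Trial design:** the outcome of Phase three is "comparisons of baseline and four-month follow-up assessments between the intervention group, which receives CGT apps, and the control group".
- **Phase three description:** MoCA, 3MSE and ROWMA are among the tests to be repeated and compared between the arms.
- **Outcomes, after Table 2:** the cognitive scores of both arms are to be compared at four months.

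Statistical analysis assigns repeated-measures ANOVA to within-group change for primary and secondary measurements, and independent ANOVA to comparisons between groups. It does not say which of these answers the primary question.

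**The concern.** The same three tests are given twice, four months apart. A change within one arm therefore contains whatever the app does, plus any gain from having taken the tests before, plus the natural course over four months. Without the control arm these cannot be separated.

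The problem runs in both directions. Retest gain alone could look like benefit. Conversely, Trial design states the goal as slowing decline. An intervention that held scores flat while controls fell would have succeeded, yet its own change from baseline would be about zero.

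Statistical analysis says the results will be used to estimate effect sizes for a full-scale trial. If the within-arm change is the figure carried forward, that sample size would rest on a contaminated estimate. A protocol with two candidate primary contrasts also leaves the choice open until the data are seen.

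**Working it through.** **The plan's own figure.** The section on participant withdrawal gives 30 intervention patients, up to 20% dropout and at least 25 completers. The 30 reproduces as 25 × 1.2 = 30. Dividing instead gives 25 / 0.8 = 31.25, and 30 less 20% leaves 24. The difference is small and the point does not depend on it. No alpha, SD, effect size or power is stated, so there is nothing else to reproduce.

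**Inputs.**
- From the protocol: n = 25 completers in the intervention arm; 25 controls; both arms assessed at both times.
- Assumed: two-sided 5% test; no app effect; test-retest correlation r of 0.5, 0.7 or 0.8; retest gain g of 0.1, 0.2 or 0.3 SD of the score; independent participants.

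**False improvement in the within-arm test.** With two time points, repeated-measures ANOVA is equivalent to the paired t-test.

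- SD of change = SD × √(2(1 − r)), which is 1.000, 0.775 and 0.632 SD for r = 0.5, 0.7 and 0.8.
- Noncentrality = g × √25 / √(2(1 − r)). Example: r = 0.7 and g = 0.2 give 0.2 × 5 / 0.775 = 1.29.
- Probability of a significant improvement = P(T > 2.064), where T is noncentral t on 24 df.

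| r | g = 0.1 SD | g = 0.2 SD | g = 0.3 SD |
|---|---|---|---|
| 0.5 | 7% | 16% | 30% |
| 0.7 | 9% | 24% | 46% |
| 0.8 | 12% | 33% | 62% |

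The nominal rate in this direction is 2.5%. The figures are per test, and there are three tests.

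**The same shift in both arms.** Express the shared shift in SD-of-change units. The within-arm test is significant (two-sided) in 16% of trials at a shift of 0.2, 30% at 0.3 and 67% at 0.5. In a 20,000-run simulation with 25 per arm, a between-arm test on change stayed at 4.9% to 5.1% for shifts from −0.3 to 0.5.

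**The opposite error.** If the app exactly halts a decline, the expected within-arm change is zero. The chance of a significant improvement is then 2.5%, however far controls fall. The between-arm test has 41% power when controls fall by 0.5 SD of change and 79% when they fall by 0.8.

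**Cost in precision.**
- Within-arm 95% CI half-width: 2.064 / √25 = 0.41 SD of change.
- Between-arm half-width: 2.011 × √(2/25) = 0.57 SD of change.
- Power for a true 0.5 SD effect with no shared shift: 67% within arm, 41% between arms.

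**The case against.** A reader might infer from the Outcomes sentence that the control arm plays no part in the cognitive answer, or that the protocol will take the before-after change as the app effect. The article does not support either inference. Both arms take the same tests at both times, several sections plan a between-arm cognitive comparison, and no section says the within-arm change alone will be interpreted as the effect. The defect is a contradictory definition, not an uncontrolled trial.

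Regression to the mean is also tempting to add. Table 1 sets no cognitive score threshold for entry, so there is no stated reason to expect it in the overall mean change.

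Three further objections carry weight:

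- **The percentages are illustrative.** The retest gains, correlations and alpha come from no section of the protocol. Natural decline would work against retest gain and lower the false-improvement rates.
- **The trial is a pilot.** Its stated goal is to collect initial data and assess procedures, and the step to further funding is tied to feasibility and acceptability. This limits the weight of any cognitive test.
- **The between-arm contrast is not clean either.** The research team allocates whole dialysis routes, six in all, so differences between routes and clustering remain.

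None of these settles which contrast is primary. The question still matters because effect sizes for the next trial are to come from these data.

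**Conclusion.** The concern holds as an inconsistency. The formal definition of the primary outcome is a single-arm change from baseline, while four other places in the article describe a comparison between arms. The analysis section plans both kinds of test and ranks neither. The contrast with the secondary-outcome sentence makes it hard to treat the wording as shorthand.

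An analyst who follows the definition literally would report a primary result that cannot separate the app from retest gain or natural course, and that could miss slowed decline. The illustrative false-improvement rate is about 7% to 62% per test. It depends wholly on the assumed gain and correlation, and on no offsetting decline. That a within-arm change has no control for shared shifts does not depend on those assumptions.

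**What to change.** In Outcomes and Statistical analysis, define the primary cognitive outcome for each test as the intervention-minus-control difference in the four-month score, adjusted for the baseline score, and report it with a 95% CI. The article already describes a comparison between arms; the baseline adjustment and the interval are additions. Keep the within-arm change as description, with no test and no claim of effect.

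The change is to wording only, because both arms are already assessed at both times. The price is precision: a half-width of about 0.57 against 0.41 SD of change with 25 per arm. That comparison uses unadjusted change scores and independent participants, and allocation by route would widen the interval further. Since the contrast also remains open to differences between routes, the text should call it a preliminary estimate.

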### Statistical analysis

Given the pilot nature of this study, our sample size is not based on formal power calculations. Instead, it is pragmatically determined by the number of eligible patients in our dialysis unit. The results will be used to estimate effect sizes and inform sample size calculations for a future, full-scale randomised controlled trial.

In Phase three, data will be analysed to test the effect of CGT intervention on the scores of baseline and follow-up assessments. All data analyses will be conducted in IBM SPSS Statistics for Windows, version 27.0 (or higher) software. Data will be directly entered into Microsoft Office Excel spreadsheets (version 2202) by investigators and study staff using all standard data management procedures. Descriptive statistics will be calculated according to the normality assumption, with means and standard deviations reported for normally distributed data, and medians and interquartile ranges reported for non-normally distributed data. Within-group comparisons between baseline and follow-up assessments for primary and secondary measurements will be analysed using repeated-measures analysis of variance (ANOVA). In contrast, independent ANOVA will be used for between-group comparisons. For additional explorative analyses, correlation and regression models can be used to analyse the effects of other factors (e.g. age, gender) on the cognitive decline between the baseline and follow-up assessments.

In addition to the primary and secondary outcome analyses, a sub-group analysis will be performed to explore the potential effects of the CGT intervention based on participants’ baseline memory function and executive function. Participants will be stratified into subgroups based on their performance on the cognitive test scores, and the intervention effects will be compared between these subgroups. This exploratory analysis may help to identify which patients are most likely to benefit from the CGT intervention and guide future research in this area.

No formal power calculation was conducted because this pilot study focuses on evaluating the feasibility and acceptability of using CGT apps in individuals undergoing haemodialysis. The primary goal of this pilot trial is to collect initial data and assess the study procedures rather than testing a specific hypothesis with a predetermined level of statistical power. The results from this pilot study will guide the design and sample size calculation for a future, larger scale definitive randomised controlled trial.

While our sample size limits a detailed analysis of the impact of different dialysis schedules, we will collect data on each participant’s schedule (Monday-Wednesday-Friday or Tuesday-Thursday-Saturday, and shift time). We will conduct exploratory analyses to examine potential associations between schedule and outcomes. This information will be valuable for designing a larger future trial where schedule effects could be more robustly analysed.

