### Trial population and recruitment

The investigators will collaborate with local representatives of KPAs and people within the kidney service to recruit the participants who are currently receiving haemodialysis therapy at the Hull University Teaching Hospitals NHS Trust kidney service. Healthcare professionals at the kidney unit will discuss study participation with the patients before obtaining formal informed consent.

The investigators will give potential participants a letter and the trial participant information sheet. Consent for participation in the trial will be collected via a formal Informed Consent Form authored by the investigators; the consent form will check candidates suitability against both inclusion and exclusion criteria (fit recruitment profile/ confirmation that situations have not changed since recruitment), and outline the specifics of the trial, what activity is included in the intervention sessions (methodology outline) and how both feedback and personal data will be collected and processed. All inclusion and exclusion criteria are given in Table 1. For Phase two, the focus group/semi-structured interview sessions will be conducted with people who meet the same inclusion and exclusion criteria as the main trial participants (Table 1), ensuring consistency in the target population.

**Table 1 Tab1:** Inclusion and exclusion criteria of the proposed trial.

Inclusion criteria	Exclusion criteria
18 years or older	Less than 18 years of age
regular haemodialysis therapy for at least three months	Haemodialysis for less than three months
	Planned kidney transplant within the intervention period
	Active malignancy
	Inability to complete study assessments from the clinical perspective
	Inability to complete the interventions from the clinical perspective
	Inability to use tablet and the CGT app Inability to consent to study

As this is a pilot study, the sample size is determined by the number of eligible patients in the participating haemodialysis unit. While formal age-matching between the intervention and control groups is not feasible due to the small sample size, we will strive for balance in baseline characteristics through randomisation. The primary aim of this pilot study is to assess feasibility and gather preliminary data to inform a future, larger randomised controlled trial.

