### Participant withdrawal

Participants have the right to withdraw from treatment and/or the trial at any time. Participants will remain in the trial for follow-up unless they request to fully withdraw. All data up to the point of withdrawal will be stored, after withdrawal participant’s data will be destroyed and will not be included in the final dataset.

In the event of participant withdrawal, the Investigator(s) will promptly explain to the participant that their involvement in the trial will discontinue and explain why.

For Phase two, the focus group/semi-structured interview sessions will be conducted with people who are currently receiving haemodialysis therapy. After receiving feedback from the focus groups/semi-structured interviews, a finalist of CGT apps will be determined to be used during haemodialysis sessions.

Fifty-five people attending haemodialysis therapy will be recruited for Phase three. The intervention arm includes 30 patients to account for up to a 20% potential dropout and ensure at least 25 can complete the study. The control arm will have 25 haemodialysis patients with usual care. All participants will complete assessments at baseline and at approximately four months (± two weeks).

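### The named ANOVAs and the withdrawal rule leave a completers-only cognitive result, although the plan allows for up to 20% loss in the intervention arm

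*Protocol article*

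**What the plan says.** All references are to the protocol article.

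- **Analysis (Statistical analysis).** "Within-group comparisons between baseline and follow-up assessments for primary and secondary measurements will be analysed using repeated-measures analysis of variance (ANOVA". For the arms: "In contrast, independent ANOVA will be used for between-group comparisons". The section does not say whether the independent ANOVA is run on the four-month score or on change. It says the results will supply effect sizes for a definitive trial.
- **Primary outcome (Outcomes).** "The primary outcome will be a change in cognitive test results (MoCA, 3MSE and ROWMA) of the intervention group", at about four months against baseline. This is a within-arm change. The same section later describes comparing the two arms' scores at four months.
- **Numbers (Participant withdrawal).** Phase three is to enrol 55 people. On the larger arm the section says: "The intervention arm includes 30 patients to account for up to a 20% potential dropout and ensure at least 25 can complete the study". Controls number 25, and no allowance for loss is stated for them. Assessments take place at baseline and about four months only.
- **Withdrawal (Participant withdrawal).** "Participants will remain in the trial for follow-up unless they request to fully withdraw". The next sentence says data collected up to withdrawal are stored, and then that a withdrawn participant's data are destroyed and left out of the final dataset.
- **Allocation (Randomisation).** Whole dialysis routes are assigned to an arm by the research team.

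**The concern.** With one baseline and one follow-up test, a conventional repeated-measures ANOVA, or an ANOVA on change or on the four-month score, has nothing to analyse for a participant without the second test. That participant's baseline is discarded too. The withdrawal rule goes further: read literally, it deletes the baseline of anyone who fully withdraws, so no other analysis could recover it and those lost could not be described.

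Loss of this kind matters if it is linked to cognition. Table 1 makes "Inability to complete study assessments from the clinical perspective" an exclusion at entry. It is reasonable, though an inference, that the same state may arise during four months of follow-up. If so, the participants who remain do not represent the arm that was recruited.

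Two results are at stake. One is the intervention arm's own change, where no control comparison can cancel the selection. The other is the between-arm estimate that the pilot is meant to hand on.

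**Working it through.** **1. The plan's own figure.** 25 × 1.20 = 30 reproduces the intervention-arm size. Allowing for 20% loss by division gives 25 / 0.80 = 31.25, so 32. At the full 20%, 30 × 0.80 = 24 remain, one short of the 25 intended. The analysed set would be 24 + 25 = 49 of 55 with no control loss, or 24 + 20 = 44 with 20% control loss.

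**2. Inputs for the bias check.** From the documents: up to 20% loss in the intervention arm, and two assessments. Assumed, because the documents give none of these: correlation r between baseline and four-month score of 0.6 to 0.8; log odds of loss of 0.5, 1.0 or 1.5 per SD lower score (odds ratios 1.6 to 4.5); control loss of 0%, 10% or 20%. There is no true effect, and scores have SD 1.

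**3. Selection shift.** Let m be the amount by which completers' mean exceeds that of the full arm on the score that drives loss. Simulation (1,000,000 pairs) with 20% logistic loss gives m of about 0.095, 0.172 and 0.225 for the three log odds.

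**4. Loss driven by baseline, 20% v 0%.**
- Four-month difference = r × m: from 0.6 × 0.095 = +0.06 to 0.8 × 0.225 = +0.18 SD.
- Difference in change = (r − 1) × m: from −0.2 × 0.095 = −0.02 to −0.4 × 0.225 = −0.09 SD.
- Likelihood model using all baselines: 0.00.

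The two ways of running the independent ANOVA therefore err in opposite directions.

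**5. Loss driven by the unseen four-month score, 20% v 0%.**
- Four-month difference = m: +0.10 to +0.23 SD.
- Difference in change = (1 − r) × m: from 0.2 × 0.095 = +0.02 to 0.4 × 0.225 = +0.09 SD.
- Likelihood model: about +0.04 to +0.15 SD, which is better than the four-month ANOVA but worse than the change ANOVA.

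**6. Control loss.** At r = 0.7 and log odds 1.0, 10% control loss roughly halves the between-arm bias (four-month-driven loss: 0.17 falls to 0.08 SD). Equal 20% loss with the same mechanism brings it to zero. The intervention arm's own change is unaffected by what happens to controls: its bias stays at 0.3 × 0.172 = 0.05 SD, negative in step 4 and positive in step 5.

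**7. Against precision.** The standard error of the four-month difference is √(1/24 + 1/25) = 0.29 SD, so that bias is 0.06/0.29 = 0.2 to 0.23/0.29 = 0.8 of a standard error. For the difference in change, the largest bias occurs at r = 0.6. The change score then has SD √(2 × 0.4) = 0.89, the standard error is 0.89 × 0.29 = 0.26, and 0.09/0.26 = 0.35.

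**8. A more direct mechanism.** Suppose staying in the trial is itself correlated with change (assumed correlation 0.3 or 0.5). The completers' mean change is then shifted by +0.11 or +0.18 SD of the change score. In simulation with 6 of 30 lost, the within-arm test's two-sided false-positive rate was 8.2% or 14.2% instead of 5%, whatever the control loss. With correlation −0.3, the between-arm bias was −0.10 SD, against the apps.

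**The case against.** **Missing-data rules belong in the analysis plan.** This stands in part. An analysis plan may exist, nothing in the article forbids imputation before the ANOVA, and the lack of an imputation rule is not an error. What remains is on the page: the named methods, and a rule that takes withdrawn participants out of the dataset.

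**A reader might infer that loss will be 20% v 0%.** The documents do not support that. Thirty against 25 is a recruitment allowance, not a forecast that no control will be lost. The article does not list death or unplanned transplant as ways off the endpoint, and neither would be peculiar to one arm. Participants who only stop using the apps remain in follow-up, so not every dropout from the intervention is lost to analysis.

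**A reader might infer that the result will favour the apps.** That is not supported either. Baseline-driven loss biases the difference in change against the apps, the opposite mechanism reverses the sign, and equal loss with the same mechanism removes the between-arm bias.

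**A mixed model brings its own risk.** This is correct for a model without an arm term, which forces equal baselines. Routes are allocated by the research team, so that assumption is not earned. With a persistent arm difference of 0.3 SD and r = 0.7 (both assumed), it would give 0.3 × (1 − 0.7) = +0.09 SD with no effect and no loss. The model needs an arm term.

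**This is a pilot.** True, and retention is already a feasibility outcome. That limits the severity, but the article does plan to pass on effect sizes.

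**Conclusion.** The point holds in a limited form. Followed as written, the two ANOVAs and the withdrawal rule give completers-only cognitive and quality-of-life results in a trial that allows for up to 20% loss in one arm. If loss is related to cognition, the stated primary outcome is biased whatever happens to controls. The between-arm estimate is biased only if loss, or its mechanism, differs by arm.

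Under the two score-driven mechanisms with 20% v 0% loss, the size is about +0.06 to +0.23 SD for the four-month difference and −0.09 to +0.09 SD for the difference in change. Both are below one standard error. These figures rest on assumed correlations, dropout odds and control loss, and neither the size nor the direction can be predicted from the documents. The change is worth making because it is cheap and protects the estimate the pilot is meant to supply. It is not a threat to the feasibility aims.

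**What to change.** 1. **Participant withdrawal.** Reconcile the two parts of the sentence on stored and destroyed data, so that data collected before withdrawal are kept and analysed where consent allows. Without this, withdrawn participants' baselines cannot enter any model.
2. **Statistical analysis.** Make the main cognitive and quality-of-life analysis one likelihood-based mixed model (available in SPSS), with baseline and four-month scores as outcomes and terms for arm, time and arm-by-time. Include every participant with a retained baseline score, and do not constrain the arms to equal baselines. Keep the ANOVAs as supportive, and say whether the independent ANOVA uses the four-month score or change.
3. **Sensitivity and reporting.** The model remains biased if loss depends on the unseen four-month score. Add one sensitivity analysis that shifts the scores of those not testable at four months, for example by −0.5 and −1 SD. Report by arm the reasons for missing tests and the baseline scores of those lost.

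The cost is a change of wording in two sections, a missing-at-random assumption for the main model and one extra table. No new patients or visits are needed.
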